## Methods

### Study Design

The proposed hybrid type 1 study is a single-site, 2-arm, single-blind RCT designed to simultaneously assess (1) feasibility and acceptability of an RCT of stepped-care web-based parent support (ie, adherence, fidelity, costs, and acceptability) and (2) efficacy of the stepped-care I-InTERACT-North program in improving positive parenting skills and child behavior among families of children with CHD.

Hypothesis 1: based on our pilot data, we hypothesize that the stepped-care program will demonstrate program feasibility (ie, adherence and fidelity, >70%) and high acceptability (ie, based on postintervention program ratings, thematic analysis of feedback, >90%) across CHD families.

Hypothesis 2: we hypothesize that positive parenting skills and child behavior will improve at the end of the treatment among participants in the treatment arm compared to CAU and remain improved compared with CAU at 12 months. We consider positive parenting skills as the primary proximal outcome and child behavior (co–primary outcome) as mediated by improvements in parenting. We also consider secondary outcome changes in parent mental health and family quality of life.

After completion of baseline measures, families will be randomized to receive CAU or active I-InTERACT-North stepped-care treatment. Randomization will be stratified by sex assigned at birth (male, female) and baseline child behavior severity (Eyberg Child Behavior Inventory [ECBI] intensity *t* score above or below cutoff of 60) and executed by a computerized randomization system on REDCap (Research Electronic Data Capture; Vanderbilt University) [30]. Families in both conditions will complete follow-up measures at 3 months, 6 months, and 12 months postbaseline (Figure 1). Families randomized to CAU will receive no direct parent treatment other than clinical care provided in cardiac follow-up (ie, child assessment and consultation), which will be documented accordingly. The CAU families will be offered I-InTERACT-North after completion of their 12-month follow-up measurements. Participants cannot be blinded to their condition, but they will be blinded to primary outcomes and hypotheses. Independent study staff responsible for coding the primary outcomes (ie, positive parenting skills) will be blind to participant allocation, outcomes, and baseline or follow-up status.

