### Sample Size and Power Analysis

Based on the size of the research registries available for recruitment and pilot estimates of consent rate (70%), we anticipate that 382 families will consent to participate in the RCT. Using pilot estimates of adherence rate (86%), we anticipate that 328, 282, and 244 families will complete the 3-month, 6-month, and 12-month follow-up measurements, respectively. Samples of 122 participants in each condition at 12 months postbaseline will provide >95% power to detect an effect size of 0.64, which is a medium to large effect size conservatively based on our pilot data. This sample size also achieves a power of 95% for subgroup analyses with subgroups with a split of 50%, which is consistent with or close to that of our pilot data.

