#### Primary Efficacy Analysis

Primary efficacy analysis will be conducted using an intent-to-treat approach. Generalized estimating equations for longitudinal count-level data having a Poisson distribution will be used to examine changes on the DPICS positive parenting composite. We will account for missing data with the Kenward-Roger degrees of freedom command and using a random intercept with the appropriate covariance structure to allow for unbalanced covariance matrices. The main effect of the program on positive parenting skills will be tested by linear contrast of adjusted DPICS mean change scores from baseline to 3 months between groups. We will also refit the regression model to include stratification variables (sex, baseline behavior intensity) and intervention step as moderators of the effect of treatment. The co–primary outcome of child behavior, as well as continuous secondary outcomes of quality of life and parent mental health, will be tested with repeated-measures analyses including condition, stratification variables (ie, sex assigned at birth and baseline child behavior severity), intervention step, and their interactions as fixed effects. Individual subjects as random effects will be adjusted to the data [43,44]. Sensitivity analyses will be carried out to replicate the analyses [29] from the initial adaptation of the I-InTERACT-North program into a stepped-care model for children with neurological risk, examining the preliminary efficacy in changes in positive parenting skills and child behavior based on intervention step. Finally, we will replicate the analyses conducted by Wade and colleagues [25] in the RCT of the original version of I-InTERACT for children with TBI, testing a moderated mediation model using regression-based process modeling to assess the indirect effects of treatment group on child behavior at 12-month follow-up through the change score for positive parenting.

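### The only planned mediation test needs a 12-month child-behavior score that 36% of families are expected to lack, and the stated missing-data provision does not extend to it

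*Protocol article*

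**What the plan says.** Study Design, under Hypothesis 2, treats "child behavior (co–primary outcome) as mediated by improvements in parenting". Primary Efficacy Analysis opens with "Primary efficacy analysis will be conducted using an intent-to-treat approach" and then sets out three layers:

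- a longitudinal count model for the DPICS composite, with missing data addressed through Kenward-Roger degrees of freedom and a random intercept;
- repeated-measures models for the ECBI and the continuous secondary outcomes;
- last, a replication of an earlier trial's analysis: "testing a moderated mediation model using regression-based process modeling to assess the indirect effects of treatment group on child behavior at 12-month follow-up". The mediator is the change score for positive parenting, and the article does not say between which visits.

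Planned Statistical Analysis names SPSS for the quantitative work. Table 1 schedules both DPICS and ECBI at baseline and at 3, 6 and 12 months. Sample Size and Power Analysis states "we anticipate that 382 families will consent to participate in the RCT" and then "we anticipate that 328, 282, and 244 families will complete the 3-month, 6-month, and 12-month follow-up measurements, respectively", applying an 86% rate at each visit.

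**The concern.** A process model built from ordinary regressions needs the mediator and the 12-month outcome for every family it uses. A random intercept and Kenward-Roger degrees of freedom help only where a family contributes repeated outcomes to one model, and this model has one outcome per family. Run as described with nothing added, it is a complete-case analysis, although it sits under a heading that commits to intent-to-treat.

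This is the only analysis that addresses mediation, and the Discussion and Conclusions look to the trial to shed light on mechanisms of change. Dropout that differs by arm is plausible: treated families have sessions, modules and step decisions, while control families are offered the program after their 12-month measures. If treated families with little parenting gain leave more often, the completers' treatment-to-parenting path is too large. It would then disagree with the trial's own longitudinal DPICS result.

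**Working it through.** **1. The plan's retention figures.** Inputs: 382 families and 86% per visit (Sample Size and Power Analysis).

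- 3 months: 382 × 0.86 = 328.5 (stated 328)
- 6 months: 382 × 0.86² = 282.5 (stated 282)
- 12 months: 382 × 0.86³ = 243.0 (stated 244)

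The figures reproduce within rounding. The plan also says "Samples of 122 participants in each condition at 12 months postbaseline will provide >95% power to detect an effect size of 0.64". With two-sided α = 0.05 (assumed, as none is stated), power is 99.9%, which agrees. That statement does not concern the indirect effect.

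**2. Missing outcome.** 382 − 244 = 138, and 138/382 = 36.1% (36.4% from 1 − 0.86³). A complete-case mediation model has at most 244 families.

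**3. Precision under random dropout.** With unit SD and equal arms, the SE of the treatment-to-parenting path is 2/√n.

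- n = 244: 2/√244 = 0.128
- n = 328: 2/√328 = 0.110, about 14% smaller

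This comparison assumes that the mediator is change to 3 months. In that case 328 − 244 = 84 families with an observed mediator are left out.

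**4. Bias, large-sample illustration.** All coefficients are assumed.

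- Mediator = 0.64 × arm + noise (SD 1)
- 3-month ECBI = 0.5 × baseline − 0.3 × mediator + noise (SD 0.7)
- 12-month ECBI = 0.3 × baseline − 0.2 × mediator + 0.5 × 3-month ECBI + noise (SD 0.6)

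True indirect effect: 0.64 × (−0.2 − 0.5 × 0.3) = 0.64 × (−0.35) = −0.224. Missingness is set to about 36%, with log-odds of 1 per unit of the driving variable, and baseline ECBI is in the fitted model.

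| Dropout mechanism | Full data | Completers | Change in size |
|---|---|---|---|
| Random | −0.224 | −0.225 | about nil |
| Depends on baseline ECBI | −0.222 | −0.221 | about nil |
| Depends on 3-month ECBI, same in both arms | −0.225 | −0.214 | about 5% smaller |
| Depends on 3-month ECBI, opposite directions by arm | −0.224 | −0.283 | about 26% larger |
| Low-skill families leave the treated arm only | −0.223 | −0.315 | about 41% larger |

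In the last two rows the inflation comes from the treatment-to-parenting path (0.84 and 0.90 instead of 0.64). The parenting-to-behavior path hardly moves (−0.34 and −0.35 against −0.35).

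**5. Bias at the trial's size.** 382 families, 14% loss per interval, 1,500 replicates, path 0.64, true indirect effect −0.19 or −0.10. Dropout after 3 months in treated families depends on parenting gain and ECBI.

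- Log-odds −0.5 and +0.25 per SD: completer path 0.79, indirect effect about 20% too large.
- Log-odds −1.0 and +0.5 per SD: completer path 0.90, indirect effect about 30-37% too large.
- Multiple imputation using the 3- and 6-month scores: path 0.64, indirect effect −0.19 or −0.095, essentially unbiased. This is partly by construction, because dropout was generated from variables in the imputation model.

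**The case against.** A reader might infer that the plan drops the 138 families and that the indirect effect will therefore be a biased completer estimate. The document supports neither step. It does not mention listwise deletion, and it does not rule out imputation before the model is fitted. Complete-case use is the ordinary default of the named method, not a stated rule. A full protocol or analysis plan that is not shown, or the replicated trial's own handling of missing data, could settle the matter. Nor is bias certain: the plan gives one retention rate, with nothing by arm or by outcome, and several plausible mechanisms produce almost no bias or slight attenuation.

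The analysis is also a closing replication. Hypothesis 2 is tested by the longitudinal DPICS and ECBI models, which can use partial follow-up, and the 3- and 6-month ECBI scores are used there. The trial is sized on 122 per arm at 12 months, so 244 is a number the plan already expects. If the mediator is change to 12 months, families without that visit lack the mediator as well, and the 84-family figure falls away.

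All of this stands, and it limits the point. It does not remove it: the article names a single-outcome method, expects 36% of outcomes to be missing, and offers only a provision that cannot work in that method. The remedy is a better estimator using scores already scheduled, not just a request to write down a policy.

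**Conclusion.** The point holds in conditional form. As described, and without an added missing-data method, the mediation model will use at most 244 of 382 families. The 36% is firm on the plan's own figures, assuming that families once lost stay lost, as the compounding implies. The 14% difference in SE applies to the treatment-to-parenting path and requires a 3-month mediator. The bias figures are a range under assumed mechanisms, not a forecast: near nil if dropout is random or driven by baseline covariates in the model, and about 20-40% inflation if it differs by arm in the ways simulated. The between-group conclusions of Hypothesis 2 are unaffected. This is a worthwhile, inexpensive improvement to a supporting analysis, not a flaw in the trial's main comparison.

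**What to change.** In Primary Efficacy Analysis, keep the same moderated mediation paths but fit them on all randomized families. Use full-information maximum likelihood, or multiple imputation by arm that includes baseline, 3-month and 6-month ECBI, all DPICS scores and the stratification variables. Name the visits that define the parenting change score. Report the regression-based process model on completers alongside, as a sensitivity or replication analysis.

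The cost is a sentence or two of text and modest analysis work, with no new data and no more families. The small downside is that the lead mediation result may not be computed exactly as in the earlier trial. With follow-up planned to January 2029, the method can still be fixed before results are known.

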## Results

The time period for this study is 5 years, having commenced alongside funding from the Canadian Institutes of Health Research (FRN186222) in February 2023 and research ethics board approval (Figure 4) in August 2023. Hiring and training of I-InTERACT-North therapists spanned April to August 2023, with a total of 13 active therapists as of April 2024. Recruitment began in February 2024. As of September 2024, 24 families have enrolled in the trial, and 55.0% (11/20) families randomized were assigned to the I-InTERACT-North condition. Therapy delivery began in March 2024 and is expected to continue until late 2028. Based on our pilot data and consent rate to date of 65%, we anticipate recruitment to continue through January 2028, with intervention and follow-up concluding in January 2029. An additional 8 months will be allocated toward data analyses and end-of-grant knowledge dissemination including publications in peer-reviewed journals and presentations at international conferences by August 2029.

Integrated knowledge translation will span the 5-year study period, including community partner engagement, family advisory feedback, preparation for knowledge dissemination, multisite collaborations, and preparation for larger-scale multisite grant applications nearing the study end date. To date, knowledge translation has included presentation and discussion with clinical teams in CHD clinics as well as parent and family advisors at SickKids. In February 2024, we consulted with a parent and family advisory council comprising parents and caregivers of children with CHD followed at The Hospital for Sick Children. Members endorsed the strong need for mental health supports, especially in middle childhood as mental health needs become apparent following stressful medical complexities in the early years. Parents also highlighted the lack of accessible mental health programming available, with one parent writing “When my daughter needed this 5 years ago nothing really existed at SickKids. We had to find support in the community which is also really challenging!” Similarly, nurses in the cardiac follow-up clinic at SickKids celebrated the acknowledgment of mental health needs for families and children with CHD and the availability of a free, adaptable, virtual program at SickKids.

**Figure 4 figure4:**
[figure not shown]
Study timeline. CAU: care as usual; I-InTERACT: Internet-based Interacting Together Everyday Recovery from Traumatic Brain Injury; REB: research ethics board.

## Discussion

### Principal Findings

This study protocol presents the rationale and details of a stepped-care web-based support program for parents of children with CHD and describes the trial that will be used to assess the feasibility, acceptability, and efficacy of I-InTERACT-North. To our knowledge, this is the only RCT to examine the efficacy of a virtual positive parenting program among families of children with CHD, contributing to the well-recognized gaps in mental health support in pediatric cardiology follow-up programs. As mortality from CHD has decreased and focus has shifted toward addressing developmental and mental health morbidities, the need for intervention programs has become a priority [45], and parents of children with CHD prioritize mental health needs among the most important factors in optimizing their child’s and family’s well-being [7,8,14,46]. However, existing CHD literature regarding intervention supports has concentrated primarily on early developmental services, psychopharmacological treatment, and the need for academic supports, with limited psychosocial supports available [47]. Thus, the critical need for accessible, evidence-based, and personalized mental health supports, taken together with evidence supporting positive parenting as a modifiable determinant of health and the relationship between psychosocial support and psychological distress among families of children with CHD [48], underlines the need for this trial.

This trial aligns with the Cardiac Neurodevelopmental Outcome Collaborative’s clinically informed research agenda to “adapt existing interventions for individuals with CHD” to advance this field of research and elucidate the impact of psychosocial interventions in CHD populations [49]. The hybrid type 1 design was selected purposefully to simultaneously test both intervention efficacy and implementation outcomes, thereby shortening the time needed to study both [50]. The hybrid design is preferred when evidence exists in support of the intervention (as is the case with I-InTERACT-North) and when there is momentum for implementation [50,51]. Examining stepped care also increases potential for improved service delivery and access for at-risk and diverse families traditionally underrepresented in mental health research.

### Comparison With Prior Works

Despite significant empirical support for parent management training and behavioral family interventions for children and adolescents with developmental and behavioral challenges [52-55], few studies have specifically targeted CHD populations. The work of Christopher McCusker and his team at The Royal Belfast Hospital for Sick Children, Northern Ireland, has pioneered this work across distinct age groups, with 3 Congenital Heart Disease Intervention Programs (CHIP; ie, CHIP-Infant [56], CHIP-School [57], and CHIP-Family [58]). CHIP-Infant is a 6-session early intervention program that supports infant mental development, feeding, and maternal mental health, with improvements demonstrated 6 months post intervention [56]. CHIP-School and CHIP-Family are designed for school-aged children aged 4-5 and 5-8 years, respectively [57,58]. Both involve single-day parent workshops and follow-up sessions focusing on problem prevention therapy, psychoeducation, and parenting skills. CHIP-School also includes parent observation of their child safely engaging in exercise to demonstrate the child’s ability to tolerate physical activity. CHIP-Family offers child-specific cognitive-behavior therapy strategies, light exercise, and activities that promote self-esteem, emotion regulation, and problem-solving. Participation in CHIP-School was associated with improvements in maternal mental health, family functioning, and school attendance 10 months post participation but no significant improvements in child emotional and behavioral concerns. Notably, the CHIP-School study excluded children with neurodevelopmental disorders, limiting generalizability. Similarly, participation in CHIP-Family yielded no significant differences at 6-month follow-up relative to a control group in child emotional and behavioral concerns.

Taken together, the CHIP programs provide preliminary support that parent-centered interventions yield valuable initial gains with respect to parental mental health and family functioning in CHD [56-58]; however, the CHIP programs primarily target parental adjustment to CHD and have a limited focus on positive parenting skills and the parent-child relationship. Similarly, other programs have also targeted the intensive early stress in infancy following CHD diagnosis or treatment for parents. Among parents of children with CHD, Li et al [59] demonstrated significant reduction in parental distress and heightened parental hope for those who underwent a solution-focused brief therapy for parental distress. Likewise, Fleck et al [60] are conducting an RCT to evaluate the efficacy of the REACH intervention for families with infants recovering from surgery for complex CHD. REACH is a home-monitoring program that combines technology and advance practice nurse monitoring to decrease parental stress and improve parental quality of life and infant stability. Although parent-focused interventions may help support early parental coping and adjustment to CHD, they may not extend to later parent-child relationship support. Other psychological intervention research with CHD populations has focused on therapy directed exclusively to children and adolescents, with little to no parental involvement and parent support [61,62].

In reviewing the landscape of the literature to date, the need for evidenced-based and personalized mental health supports for parenting and childhood behavioral problems in CHD is highlighted. Through the proposed RCT, we hope to illustrate the efficacy, feasibility, and acceptability of a novel web-based stepped-care program in improving positive parenting skills and child behavior among families of children with CHD. This trial represents the first examination of a positive parenting intervention program designed with and for families of children with CHD. Embedded within a well-established cardiac follow-up program at The Hospital for Sick Children, we have the unique opportunity to leverage a large, prospective cohort of children with a history of CHD. These children and families have longitudinal neurodevelopmental and neuroimaging data collected since birth. If the effects of the intervention are positive, as we hypothesize given previous pilot trials, this study can contribute toward widespread implementation and expansion. This implementation can span nationally and globally across various CHD cohorts, while leading the way in elucidating key mechanisms of change in treating emotional and behavioral challenges in children with CHD. As such, this study can inform the application of this program to support families of children with other early medical conditions.

### Limitations

Several limitations will be taken into consideration with respect to this clinical trial. This is a single-site study that reflects findings specific to The Hospital for Sick Children, the Toronto, Ontario, context, and a public health care system. Recruitment and intervention materials are currently available only in English, thus limiting access and generalizability to non–English-speaking families. However, several therapists are bilingual or multilingual (English and French) and interpreter services are available for recruitment, informed consent discussions, and web-based coaching sessions. Likewise, we provide families in need with tablets and web-based sticks as necessary to ensure that web-based coverage status does not pose a barrier to participation. Although the stepped-care treatment model offers increased customization and precision in our intervention approach to optimally address families’ needs, it may be challenging to elucidate differences in outcomes between those who receive exclusively an introductory appointment relative to the CAU group. It may also be difficult to control the effects of concurrent intervention services (eg, psychotherapy, rehabilitation) in evaluating the efficacy of I-InTERACT-North; however, service receipt will be explored as a secondary objective to ascertain valuable insight into additional mental health supports sought by families.

